### Monitoring

The trial will be conducted following the approved protocol. An independent committee of data and safety monitoring has been established to oversee the trial. Five chairpersons will be set up in the committee composed of independent researchers, while ensuring that committee members are not involved in the trial operation and have no conflicts of interest with this study. The data and safety monitoring committee will review and supervise the reliability and completeness of research data on the basis of ensuring the physical safety and data security of participants.

### Serious adverse events

Events that are fatal, life-threatening, disabling or incapacitating, or leading to prolonged hospital stay or malformation are defined as serious adverse events in this trial.

The patient blood pressure will be observed by follow-up, and blood samples will be tested for potassium and renal function. The main adverse events will include hypotension, hyperkalemia and renal function impairment that cannot be improved by dose reduction. Adverse reaction criteria: hyperkalemia (blood potassium > 5.5 mmol/L), hypotension (SBP < 90 mmHg or DBP < 60 mmHg), symptomatic hypotension (SBP ≥ 90 mmHg and dizziness, nausea, fatigue, syncope), and creatinine increase more than 50% will be considered as adverse events.

A detailed report will be submitted to the Medicines and Healthcare Products Regulatory Agency in a timely manner when unexpected serious adverse events occur. All patients participating in the trial will receive insurance, including additional healthcare, compensation, or damages. All adverse events which may possibly related to the trial will be recorded in the CRFs.

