#### Safety outcome

This study will also analyze the safety profile focusing on the incidence of adverse events at months 3, 6, and 12. Blood pressure will be measured and potassium and renal function will be tested during follow-up period. The main adverse events will include hypotension, hyperkalemia and renal function impairment that cannot be improved by dose reduction. Hyperkalemia (blood potassium > 5.5 mmol/L), hypotension (SBP < 90 mmHg or DBP < 60 mmHg), symptomatic hypotension (SBP ≥ 90 mmHg and dizziness, nausea, fatigue, syncope), and creatinine increase more than 50% will be considered as adverse reactions.

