### Definition

This study differentiate different cardiovascular causes for re-hospitalization into cardioversion, repeat ablation, heart failure, acute coronary syndrome, stroke or transient ischemic attack, or other cardiovascular-related diseases.

MACE are defined as heart failure, myocardial infarction, stroke, malignant arrhythmia and cardiac death. The specific definitions are as follows:
(1)Definition of heart failure: patients who had a history of HF-plausible symptoms, physical examination changes, electrocardiogram changes, cardiac ultrasound changes, and elevated serological markers of heart failure (NT-proBNP > 125 pg/ml or BNP ≥ 35 pg/ml) will be clinically diagnosed as heart failure according to the 2022 AHA/ACC/HFSA Guidelines: Management of Heart Failure. Heart failure with reduced ejection fraction (HFrEF) is classified as an LVEF ≤ 40% (17).(2)Definition of acute coronary syndrome: includes ST-segment elevation myocardial infarction (STEMI), non-ST-segment elevation myocardial infarction (NSTEMI), and unstable angina (UA) according to the guidelines for rapid diagnosis and treatment of acute coronary syndromes in emergency medicine (18).(3)The diagnosis of malignant arrhythmia (MA) refers to the diagnostic criteria for malignant arrhythmia in the 2020 American Heart Association Guidelines for Resuscitation and Emergency Cardiovascular Care (19). MA includes ventricular arrhythmias (ventricular tachycardia and ventricular fibrillation) and grade II or III atrioventricular block. Each type of MA may occur alone or in combination with other types at the same time.

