### Follow-up

After randomization, subjects will have follow-up after 3, 6 and 12 months, mainly in the outpatient clinic according to Figure 2.
(1)The survival status will be confirmed and rehospitalization and occurrence of MACE events will be requested by telephone(2)Holter electrocardiogram (>24 h), transthoracic heart color ultrasound, blood test of blood potassium and kidney function will be performed in the outpatient clinic(3)Adverse event assessment, the main adverse reactions assessed will be: hypotension, high blood potassium, impairment of renal function, as determined in the outpatient clinic(4)Medication consumption in the past will be requested by telephone;(5)Drug bottles will be collected, and the subject reminded of the importance of study medication compliance by the outpatient clinic.

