### Data collection and management

Blank case report forms (CRFs) that has been ethically approved will be used to record data for all participants. Each enrolled patient corresponds to a complete CRF, and unrecorded data will be labeled and justified. The CRFs will be entered into the scientific research platform of the First Affiliated Hospital of Shantou University Medical School in a double-entry manner by researchers. Researchers are responsible for the completeness and accuracy of the records. A CRF will include:
(1)Medical history or medical examination data(2)Informed consent of the subjects and the randomization number of this trial(3)Time of each follow-up visit and signed notes(4)Reported adverse events and their resolution or absence, including documentation such as hospitalization records, discharge summary, ECG, etc(5)Record of the medication use of the test subjects during the trial

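### The serious adverse event definition covers prolonged hospital stay but omits new inpatient admission, although patients are followed mainly as outpatients for 12 months.

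*Protocol article*

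**What the plan says.** The section Serious adverse events defines the term for this trial. Events that are "fatal, life-threatening, disabling or incapacitating, or leading to prolonged hospital stay or malformation are defined as serious adverse events". The same section attaches a reporting rule: "A detailed report will be submitted to the Medicines and Healthcare Products Regulatory Agency in a timely manner when unexpected serious adverse events occur". It also has a recording rule that does not depend on seriousness: "All adverse events which may possibly related to the trial will be recorded in the CRFs".

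Other sections bear on the same events:

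- **Withdrawal criteria:** a serious adverse event at any point in the trial is a ground for withdrawal.
- **Safety outcome:** "The main adverse events will include hypotension, hyperkalemia and renal function impairment that cannot be improved by dose reduction". Thresholds are set for potassium, blood pressure and creatinine, and incidence is analysed at months 3, 6 and 12.
- **Data collection and management:** the CRF holds "Reported adverse events and their resolution or absence, including documentation such as hospitalization records, discharge summary, ECG, etc".
- **Follow-up:** "The survival status will be confirmed and rehospitalization and occurrence of MACE events will be requested by telephone". Visits take place at 3, 6 and 12 months, mainly as outpatient visits.
- **Definition:** the re-hospitalization outcome sorts "different cardiovascular causes for re-hospitalization into cardioversion, repeat ablation, heart failure, acute coronary syndrome, stroke or transient ischemic attack", with a residual category for other cardiovascular disease.

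**The concern.** A seriousness definition should separate an abnormal finding at a clinic visit from an event that put the patient in hospital. This one does so only when a stay is prolonged. In a trial where patients go home after ablation and are then seen as outpatients, the usual route to hospital is a new admission, and the definition does not name that route.

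Two stated rules take the definition as input: the report of unexpected serious events to the regulator, and withdrawal for a serious event. Any serious-event count inherits it too, including one shown to the data monitoring committee. At stake is whether admissions caused by adverse events are classed consistently across three centers and both arms of an open-label trial.

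**Working it through.** No arithmetic applies, because the point concerns the wording of a definition. The check sets the sections side by side.

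**Step 1. List the criteria.** The definition has five limbs: death, threat to life, disability or incapacity, prolonged hospital stay, and malformation. It has no open-ended limb, such as other medically important events, through which an admission could enter.

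**Step 2. Look for the missing limb elsewhere.** Withdrawal criteria, Secondary outcome, Safety outcome, Definition, Follow-up, Data collection and management, and Statistical and analytical plans were read for another seriousness criterion. None makes a new admission serious.

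**Step 3. Compare with the timing of events.** Under Randomization and allocation, patients are randomised after ablation. Under Interventions, the dose is stepped up every 2 weeks as tolerated. Under Follow-up, contact continues to 12 months. An event that begins after discharge cannot prolong the ablation stay. It can lead only to a new admission.

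**Step 4. Apply the rule to one event in two settings.** Suppose an adverse reaction needs inpatient care, is not life-threatening, and resolves without disability.

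| Setting | Death, threat to life, disability, malformation | Prolonged stay | Class under the text |
|---|---|---|---|
| Patient still in hospital after ablation; discharge delayed | No | Yes | Serious |
| Patient at home; admitted and discharged without delay | No | No | Not serious |

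The same event is classed differently according to where the patient was when it began.

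**Step 5. See what the other provisions recover.**

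| Provision | Keeps the event on record? | Marks it as serious? |
|---|---|---|
| CRF recording of possibly related events, with hospital records | Yes | No |
| Safety outcome thresholds (potassium > 5.5 mmol/L; SBP < 90 or DBP < 60 mmHg; creatinine up more than 50%) | Yes, for the named risks | No; a clinic finding and an admission count alike |
| Telephone question on rehospitalization | Yes | No |
| Cardiovascular re-hospitalization outcome | Yes, if the cause is cardiovascular | No |

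For the last row, an admission for hypotension or syncope might fall in the residual cardiovascular category. One for hyperkalemia or renal impairment has no evident place in it.

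**Step 6. Isolate what is lost.** The event and its documents remain. What is lost is classification as serious on the ground of admission and whatever depends on it: serious-event counts and, where the event is also unexpected, the regulator report.

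**The case against.** The best case against the point has four parts.

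1. **A condensed source.** This is a journal article, and the phrase about prolonged stay may be loose wording for hospitalisation or its prolongation. That is possible, and the full protocol should be checked. But the article does not defer the definition to another document. It states one for this trial, and that text omits new admission. This lowers certainty about practice at the centers but does not remove the gap in the text.

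2. **Nothing goes unrecorded.** A reader might infer that an admitted patient's event is not reported at all. The documents contradict that. Possibly related events go into the CRF with hospital records, the three named risks are analysed as adverse events, and rehospitalization is asked about at follow-up. Nor is every such admission non-serious, since another limb of the definition may apply. This part of the objection stands in full.

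3. **The regulator report is limited to unexpected events.** Hypotension, hyperkalemia and renal impairment are named in advance as the main adverse events, and the article does not define unexpected. Adding admission as a criterion might not change regulator reporting for those three. This also stands. The effect on that report is clear only for an unanticipated reaction.

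4. **No bias between arms is shown.** A reader might infer that missed serious events fall mainly in the sacubitril/valsartan arm and make the drug look safer than it is. The documents do not support this. The definition is the same in both arms, controls also receive drug treatment, the stated safety outcome is adverse-event incidence whether or not serious, and no analysis of serious-event incidence is specified in the article. The interim review of key safety metrics is not limited to serious events either.

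**Conclusion.** The point holds in a limited form. As written, an unplanned admission for an adverse event is not serious on the ground of admission. It becomes serious only if another limb applies. Because follow-up is mainly outpatient, this is the usual form that a later hospital event will take.

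The consequence is misclassification rather than loss of data. Such events can be left out of serious-event counts and, if unexpected, out of the regulator report. The primary outcome analysis and the analysis of the named adverse events do not use the seriousness definition.

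The size cannot be given as a number. The documents contain no admission rate for either arm of 231 patients, and any count would rest on an assumed rate with no source in them.

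The conclusion assumes that the article's wording is the operative definition. If the full protocol already lists inpatient hospitalisation, only the article's wording needs correcting. Otherwise the definition should be amended, since it gives the wrong class to a foreseeable kind of event and the records needed to put it right are already collected.

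**What to change.** - Define serious events to include those that require inpatient hospitalisation or prolong an existing one, alongside the present limbs. If the full protocol already does so, cite it and correct the article's wording.
- Exempt admissions planned before the event, and state how that is documented.
- Apply the rule identically in both arms and at all three centers, and carry it through to the regulator report and to any serious-event listing for the monitoring committee.
- Reclassify admissions already recorded, using the hospital records and discharge summaries in the CRFs.
- Reconcile the change with Withdrawal criteria in the same amendment. A wider definition would otherwise bring more patients under that criterion, including patients whose unplanned cardiovascular re-hospitalization is itself a study outcome, and could end their follow-up. The two sections must be made consistent so that reclassification does not in itself remove patients from outcome follow-up.

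The cost is an amendment to the definition, a linked amendment to Withdrawal criteria, an updated event form and somewhat more serious-event reports to process. The section Auditing and amendment provides the route, and Trial status describes the trial as still recruiting.

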### Blinding

This trial is designed as an open label. Trial participants and care givers will not be blinded to the group assignment while the investigator or other relevant personnel will not be made aware of the information about the treatment subgroup to which they are assigned until the order of enrollment/randomization of the subjects has been confirmed. Data analysts and outcome evaluator will remain blinded to minimize trial bias.

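### As worded, the adverse event recording rule depends on possible relatedness to the trial, conflicts with the CRF content list, and in an open-label trial can make recorded incidence depend on attribution

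*Protocol article*

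**What the plan says.** Two places in the protocol article say what goes into the CRF.

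- Serious adverse events: "All adverse events which may possibly related to the trial will be recorded in the CRFs".
- Data collection and management, in the list of CRF contents: "Reported adverse events and their resolution or absence, including documentation such as hospitalization records, discharge summary, ECG, etc". No relatedness condition appears there.

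The outcome that depends on these records is in the section Safety outcome: "This study will also analyze the safety profile focusing on the incidence of adverse events at months 3, 6, and 12". On knowledge of assignment, the Blinding section says "Trial participants and care givers will not be blinded to the group assignment". It adds that data analysts and the outcome evaluator stay blinded, but does not say who judges whether an adverse event is related.

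The same numerical criteria appear under two labels. Safety outcome ends its list with "creatinine increase more than 50% will be considered as adverse reactions"; Serious adverse events ends the same list with "creatinine increase more than 50% will be considered as adverse events".

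**The concern.** In the first sentence, the clause about possible relatedness does no work unless it limits which events are entered. If sites follow it, an event reaches the CRF only after someone has formed a view on causality. In this trial one arm takes sacubitril/valsartan and the other receives conventional medication without it, and treating staff know which is which. The same complaint of dizziness or fatigue may be thought possibly related in a patient on the new drug and put down to something else in a control.

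The filter would then act on the safety outcome itself. It would also act on the safety data that the monitoring committee reviews at the interim analyses. Events never entered cannot be restored at analysis unless they can be rebuilt from other recorded data. If sites instead follow the CRF content list, there is no filter. Three centres could in good faith apply different rules.

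**Working it through.** The article states no adverse event rate, no attribution rate and no power for safety, so there is no figure of its own to reproduce. The check has two parts.

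**1. Which events the filter can reach**

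| Event type | How it is defined or found | Exposed to the filter? |
|---|---|---|
| Potassium above 5.5 mmol/L, creatinine rise above 50%, SBP below 90 or DBP below 60 mmHg, at scheduled visits | Numerical threshold (Safety outcome; Serious adverse events); measured at follow-up visits (Interventions; Follow-up), with no limit to one arm | Little: derivable if the values are captured |
| Symptomatic hypotension | SBP of at least 90 mmHg plus dizziness, nausea, fatigue or syncope | Yes: rests on reported symptoms |
| Events between visits | Depend on being reported and entered | Yes |
| All other, unsolicited events | No threshold given | Yes |
| Survival, rehospitalisation, MACE | Asked of all subjects (Follow-up) | No |

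Two features of the text further blur event and attribution. One is the change of label between adverse reaction and adverse event for identical criteria. The other is that the main adverse events are described partly by failure to improve on dose reduction, and controls have no study-drug dose to reduce.

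**2. Size, as an illustration only**

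Inputs: n = 231 per arm (Sample size). Assumed: equal true incidence p in both arms, and a probability q that an event is judged possibly related and so recorded, differing by arm.

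- Recorded rate = p × q, so recorded ratio = q(drug)/q(control), whatever p is.
- Probability of a spurious two-sided p<0.05 ≈ Φ[(d − 1.96·SE0)/SE1], where d is the difference in recorded rates a and b, SE0 = √(2m(1−m)/n) with m their mean, and SE1 = √((a(1−a)+b(1−b))/n).

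With p = 0.20:

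- q = 0.9 v 0.7: recorded 0.18 v 0.14, ratio 1.29. SE0 = √(2×0.16×0.84/231) = 0.0341; SE1 = √((0.1476+0.1204)/231) = 0.0341; Φ[(0.04−0.0669)/0.0341] = Φ(−0.79) ≈ 0.22.
- q = 0.9 v 0.5: recorded 0.18 v 0.10, ratio 1.80. SE0 = √(2×0.14×0.86/231) = 0.0323; SE1 = √((0.1476+0.0900)/231) = 0.0321; Φ[(0.08−0.0633)/0.0321] = Φ(0.52) ≈ 0.70.

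Over a range of assumptions:

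| q drug v control | Ratio | p = 10% | p = 20% | p = 30% |
|---|---|---|---|---|
| 1 v 1 (no filter) | 1.00 | 0.05 | 0.05 | 0.05 |
| 0.9 v 0.7 | 1.29 | 0.12 | 0.22 | 0.33 |
| 0.9 v 0.5 | 1.80 | 0.39 | 0.70 | 0.89 |
| 0.8 v 0.3 | 2.67 | 0.66 | 0.93 | 0.99 |

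The entries describe events wholly subject to the filter. For the scheduled laboratory and blood pressure events, the first row is the closer description.

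**The case against.** The strongest reply is that this is one loosely worded sentence in a condensed article, contradicted by the section that actually lists CRF content, and that detailed recording procedures usually sit in the full protocol. Much of that reply stands. It rules out several stronger readings that a reader might infer:

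- That the CRF records only related events. The word is not there, and the content list has no filter.
- That controls are untreated, or that their events are excluded. They receive guideline-based medication, and the condition is relation to the trial, which is wider than relation to the drug.
- That relatedness is known to be judged unblinded. No section says who judges it, and the outcome evaluator is blinded. Unblinded judgement is plausible, because care givers know the arm, but it is not documented.
- That the safety comparison as a whole is beyond repair, or that the monitoring committee has no valid control rate. The main laboratory and blood pressure events follow thresholds and scheduled measurements, and survival, rehospitalisation and MACE are collected regardless of relatedness.

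It is also fair that the statistical section names no between-arm test of adverse events, so the probabilities above describe a comparison that a reader would make rather than a planned test.

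The reply does not dispose of the point. The article does not leave the rule to another document: it states one, and states it in a form that conflicts with its own CRF list. Thresholds do not help with symptoms, unsolicited events or events between visits.

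**Conclusion.** The point holds in limited form. The two sections conflict on which adverse events are recorded, and the more specific sentence, if followed, makes recording conditional on a judgement that the article does not protect by blinding. The recorded incidence could then differ by arm without any true difference, chiefly for unsolicited events, between-visit events and symptomatic hypotension.

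The size is unknown. The illustrated ratios of 1.29 to 1.80 and spurious-significance rates of about 22% to 70% rest on an assumed 20% incidence, assumed attribution gaps, an assumed direction (more attribution in the drug arm) and a filter applied to every event counted. They show that a moderate gap is enough to matter; they do not estimate what will happen in this trial. The change should be made, because the defect lies in a stated rule and is easily removed.

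**What to change.** Replace the recording sentence under Serious adverse events with: *All adverse events in both arms will be recorded in the CRF regardless of suspected relation to the trial, with relatedness as a separate field.* Align the CRF list under Data collection and management with it, and use one label (adverse event) for the threshold criteria in both safety sections. Base the between-arm comparison on all events, and report related events descriptively.

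The cost is one sentence, one CRF field and slightly more data entry at visits that already take place. Recruitment is under way, so events left out under the present wording accumulate until the change is made.

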### Auditing and amendment

During the course of the study, representatives of the ethics committee will conduct reviews in accordance with national regulations. If there is a need to make changes to the protocol, an application will be submitted in advance to the ethics committee and regulatory agencies for approval, then recorded in the form of an amendment to the protocol.

